#### 2.5.3. Biological specimen analysis outcomes

##### 2.5.3.1. Gut microbiota composition

Each participant will be asked to collect fresh feces in the morning, load them into a sterile container, and quickly place them into an ice box. The samples will be transferred to the laboratory with an ice pack for storage at −80°C. A DNA extraction kit will be used to extract the genomic DNA from the stool samples. The DNA will be purified, and its concentration will be detected using agarose gel electrophoresis. The DNA will be diluted with sterile water to 1 ng/nl for 16S rRNA amplification and sequencing. The 16S V3–V4 region (343F and 798R) or V4–V5 region will be amplified. DNA will be sequenced on the Illumina Novaseq 6000 platform, and paired-end reads (2 × 480 bp) will be generated. Sequencing and bioinformatics analysis will be conducted using OE Biotech (Shanghai, China) on the QIIME2 platform. Sequencing data analysis will be performed on amplicon sequence variants (ASVs).

##### 2.5.3.2. Serum metabolomics

The blood sample will be collected using a butterfly needle and syringe. In total, 3 ml of blood will be drawn into a serum tube and centrifuged, and 1 ml of aliquots will be transferred into three tubes and stored in a freezer at −80°C for the analysis of metabolomics. Metabolic profiling in both electrospray ionization (ESI) positive and ESI negative ion modes will be analyzed using the AB ExionLC System (ABSCIEX, Framingham, MA) coupled with a Q-Exactive quadrupole-Orbitrap mass spectrometer with a heat ESI source (Thermo Fisher Scientific, Waltham, MA). An ACQUITY UPLC HSS T3 column (100 × 2.1 mm, 1.8 μm) will be used in the positive and negative modes. The binary gradient elution system consists of (A) water (containing 0.1% formic acid, v/v) and (B) acetonitrile (containing 0.1% formic acid, v/v). The flow rate is 0.35 ml/min, and the column temperature is 45°C. A non-targeted metabolite analysis will be performed by Luming Biological Technology Co. Ltd. (Shanghai, China).

##### 2.5.3.3. Serum zonulin

Extraction and sample preparation will be performed according to the protocol described above. The concentrations of zonulin in all samples will be measured with a commercial kit (Elabscience, Houston, TX; Diaclone, Besancon, France; Boster Biological Technology, Pleasanton, CA; R&D Systems, Minneapolis, MN) using the enzyme-linked immunosorbent assay (ELISA) method.

##### 2.5.3.4. Adverse events

Acupuncture-related adverse events, including dizziness after acupuncture, local hematoma, infection, abscesses, and other unforeseen adverse events, will be recorded during all trial periods.

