Withdrawal criteria and management	1. Misdiagnosis, violation of the inclusion criteria	
	2. Self-use of prohibited treatment	
	3. Poor cooperation with the established treatment or data collection procedures	
	4. Serious adverse events or life-threatening diseases or an acute progression of the disease occurs during the trial	
	5. Obvious discomforts arise because of the therapy	
	6. Participants request withdrawal voluntarily	

American Psychiatric Association (1).

* Healthy control matching procedure: To select a healthy control group comparable in size to the experimental group. The criteria used for this procedure (with match tolerance) are as follows: (1) age (±1 year), (2) sex (exact match), (3) family history of the psychiatric condition (exact match), (4) parental marital status (exact match), (5) mode of delivery (exact match), and (6) birth weight (±100 g). We chose to match these variables as they may be the risk factors influencing the development of tic disorders.

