### 2.4. Intervention

To ensure the optimal effects of acupuncture stimulation, all treatments were performed by one certified acupuncturist with more than 3 years of experience in practice. Before the trial, special training regarding the process and standard operation of the treatment will be provided.

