### 2.5. Outcome evaluations

The clinical evaluations include the assessment of the severity of tics and gastrointestinal symptoms. The recurrence rate will be measured after a 12-week follow-up. The primary outcome measure will be the Yale Global Tic Severity Scale (YGTSS), and secondary outcomes will consist of the gastrointestinal severity index (GSI) and the recurrence rate. Biological specimen analysis outcomes will include changes in the composition of intestinal microbiota, serum metabolites, and serum zonulin. YGTSS and GSI will be assessed at baseline and after 4 weeks when the interventions have been completed. Data relating to the recurrence rate will be collected after a 12-week follow-up. Feces and serum samples will be collected at baseline and 4 weeks after the interventions. If sample collection is concurrent with a treatment, sample collection will be performed after all interventions have been completed. The feces sample will be collected as soon as possible after completing all interventions.

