## 3. Data management and monitoring

Clinical data will be recorded in case report forms (CRFs) and imported into an electronic database. The CRFs and electronic databases will be locked after the study is completed. The personal data of all participants are kept anonymous and confidential. The original CRFs and other documents will be preserved securely at the South China Research Center for Acupuncture and Moxibustion at the Guangzhou University of Chinese Medicine. The relevant research team will supervise data quality, safety, and progress of the research.

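### Section 2.5.3.4, read literally, makes relatedness to acupuncture a condition for recording an adverse event, and it is narrower than the any-cause withdrawal criterion in Table 1

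*Protocol article*

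**What the plan says.** Section 2.5.3.4 is the only place in the Protocol article that says which adverse events are recorded: "Acupuncture-related adverse events, including dizziness after acupuncture, local hematoma, infection, abscesses, and other unforeseen adverse events, will be recorded during all trial periods".

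The withdrawal criteria in Table 1 (section 2.2) use two different scopes. Criterion 4 has no causal limit: "Serious adverse events or life-threatening diseases or an acute progression of the disease occurs during the trial". Criterion 5 is tied to treatment: "Obvious discomforts arise because of the therapy".

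Blood sampling is a study procedure. Section 2.5.3.2 states: "The blood sample will be collected using a butterfly needle and syringe". Section 2.5 gives the timing: "Feces and serum samples will be collected at baseline and 4 weeks after the interventions". Section 3.1.1 compares serum zonulin between the matched groups at baseline, so healthy controls give blood too. Under section 2.4.1 they receive no acupuncture.

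Tic severity is measured as an outcome, not as a harm: "YGTSS and GSI will be assessed at baseline and after 4 weeks when the interventions have been completed" (section 2.5). On oversight, section 3 says: "The relevant research team will supervise data quality, safety, and progress of the research". The article states no adverse event rate, no denominator for one and no analysis of one.

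**The concern.** The grammatical subject of the recording rule is the class of acupuncture-related events, and everything after the word including is a member of that class. Followed as written, the rule puts the causal judgement first and the record second. An event thought unrelated then need leave no trace in the adverse event data, and nobody can revisit that judgement later.

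This matters for three reasons.

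- The participants are children aged 4 to 18 receiving a newly developed needling therapy, and the Discussion presents tolerability in children as one of its advantages. A record already filtered by attribution is weak support for such a statement.
- With 20 treated children, an unexpected pattern is hard enough to see when everything is written down.
- Table 1 excludes children with infective diseases, and those with recent antibiotic use before fecal sampling, because of the gut microbiota. An ordinary infection during the four treatment weeks, unrelated to needling, could disturb the second set of samples. The adverse event rule does not clearly require it to be recorded.

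**Working it through.** There is no stated safety figure to reproduce, so the main check sets the passages side by side.

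**Step 1. Scope of recording against scope of withdrawal**

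| Event | Recorded under 2.5.3.4, read literally? | Withdrawal under Table 1? |
|---|---|---|
| Hematoma at a needling site | Yes, listed | Yes, if it amounts to obvious discomfort from therapy (criterion 5) |
| Serious event judged unrelated to acupuncture | Not required | Yes (criterion 4) |
| Acute progression judged unrelated to acupuncture | Not required | Yes (criterion 4) |
| Event after blood sampling, treated child | No clear place | Only if serious (criterion 4) |
| Event after blood sampling, healthy control | No clear place; an acupuncture-related event cannot occur in this group | Not stated; the criteria stand in the patient column |

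Criterion 5 is limited to discomfort caused by the therapy and criterion 4 is not. The authors thus restricted by cause where they meant to, and criterion 4 covers events of any cause. The second and third rows are the mismatch.

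**Step 2. The closing item on unforeseen events**

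- Narrow reading: it is the last member of the list of acupuncture-related events. The restriction stays.
- Wide reading: it adds unexpected events of any cause. An unrelated event that could be foreseen, such as a bruise from venepuncture, still has no clear place.

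Two sites using the two readings would fill in the same form differently.

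**Step 3. What follows for a rate**

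Let p be the all-cause proportion of treated children with an event, and s the share of those children whose event is judged related. On the narrow reading:

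recorded proportion = p × s

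This is below p whenever s is below 1. It equals the related proportion by definition. So only an all-cause rate is affected, and the direction is fixed once s is below 1.

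**Step 4. Illustration only**

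The number of treated children, 20, comes from section 2.3. The values of p and s are assumptions; the article gives neither. The chance of at least one recorded event is 1 − (1 − p × s)^20. With p = 10%:

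- s = 1: 1 − 0.90^20 = 0.88, expected children recorded 2
- s = 0.5: 1 − 0.95^20 = 0.64, expected 1
- s = 0.25: 1 − 0.975^20 = 0.40, expected 0.5

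These figures show how the mechanism works. They do not estimate its size in this trial.

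**The case against.** The strongest reply has four parts.

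**The scope may be wider than the literal reading.** The closing item can be taken to admit any unexpected event, and the list is illustrative. Worsening of tics that is linked to acupuncture is therefore already covered. This stands in part: it turns a plain restriction into an ambiguous one. It does not bring in events that are both foreseeable and judged unrelated.

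**The two passages serve different purposes.** One says who leaves the trial and the other what is listed as an adverse event outcome, so they do not strictly contradict each other. Serious events must be noticed for criterion 4 to work, and section 3 sends clinical data to case report forms that are not shown. This also stands. A reader might infer that such events, or tic worsening, go uncounted. The article does not say so: acute progression is a withdrawal reason, and tic severity is rated at week 4 in children who remain. What can be said is that the rule does not require them as safety data, and that a child withdrawn early may have no week-4 rating.

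**Nobody is named as judge of causality.** A reader might combine "all treatments were performed by one certified acupuncturist with more than 3 years of experience in practice" (section 2.4) with oversight by the research team and infer that the treating acupuncturist decides what is related. The article says only who treats. Who records and who attributes may properly be left to the full protocol, so that inference is not part of this point.

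**No harm rate is defined.** A rate reported as acupuncture-related is not biased merely because it leaves out unrelated events. This is correct, and it confines the numerical consequence to an all-cause rate.

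**Conclusion.** The point holds as a stated rule that is fixed badly, rather than as missing detail. Section 2.5.3.4 read literally makes attribution the condition for recording, is ambiguous on the wider reading, and is narrower than withdrawal criterion 4 on either. Events after blood sampling, including those in controls, have no clear place in it.

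The consequence is that an all-cause event rate could not be obtained from the recorded data. If the recorded events were presented as one, the rate would be understated to the extent that events are judged unrelated. The direction rests on two assumptions: that the literal reading is followed, and that some events are judged unrelated. The size cannot be derived from the article. A reader might try to gauge it from the number of needle punctures or from an assumed range of event rates. The first says nothing about recording scope, and the second only returns what was assumed.

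Recording everything would not establish causation either, with 20 treated children and no untreated group with tics. It would keep the evidence open to later judgement. The change should be made. It does not affect the primary analysis.

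**What to change.** Reword section 2.5.3.4 along these lines: All adverse events, whatever their cause, will be recorded in both groups from the first study procedure to the last follow-up, including events after blood sampling and events leading to withdrawal under Table 1. Relatedness to acupuncture will be judged after the event has been recorded. All-cause and acupuncture-related events will be reported separately.

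Collect the events at contacts that already exist. For treated children these are the eight sessions, the weekly contact with parents and the follow-up. For controls they are the assessment and sampling visits, since the article does not show that controls have weekly contact. State when recording ends, because section 2.5 gives a 12-week follow-up and the Discussion a 6-month one. The change concerns recording only and leaves the withdrawal criteria as they are.

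The cost is protocol wording, a revised case report form page, more minor unrelated events to log, the work of judging relatedness, and a less favourable headline rate. For children treated before the change, the report should say that the narrower rule applied to them.

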## 3. Data management and monitoring

Clinical data will be recorded in case report forms (CRFs) and imported into an electronic database. The CRFs and electronic databases will be locked after the study is completed. The personal data of all participants are kept anonymous and confidential. The original CRFs and other documents will be preserved securely at the South China Research Center for Acupuncture and Moxibustion at the Guangzhou University of Chinese Medicine. The relevant research team will supervise data quality, safety, and progress of the research.

### 3.1. Statistical analysis

#### 3.1.1. Clinical data and serum zonulin

For the clinical data, statistical analyses will be performed using SPSS Statistics 24.0 (IBM SPSS Statistics, Armonk, NY). Children in the experimental group will be matched to their peers in the healthy control group on age, sex, family history of a psychiatric condition, parental marital status, mode of delivery, and birth weight. Categorical variables will be described in the form of frequencies or percentages. Continuous variables will be presented as mean ± standard deviation or median and range. The chi-square test or Fisher's exact test will be used to compare the change in the categorical variables. Changes in YGTSS, GSI, and concentration of serum zonulin in the experimental group before and after treatment will be analyzed using paired sample *t*-test if the data conform to a normal distribution. The Wilcoxon paired-samples signed-rank test will be performed if the data do not conform to normal distribution or if there are differences in variance uniformity. Differences in concentration of serum zonulin between two matched groups at baseline will be analyzed with the above statistical methods. The results are based on two-sided tests, and a *P*-value of <0.05 will be considered statistically significant.

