## 1. Introduction

Tic disorders are neurodevelopmental disorders characterized by recurrent motor and/or vocal tics (1). The Diagnostic and Statistical Manual of Mental Disorders, Fifth Edition (DSM-5) (2), defines the following five tic disorders: provisional tic disorder; persistent (chronic) motor or vocal tic disorder; Tourette's disorder (also known as Tourette's syndrome [TS]); other specified tic disorder; and unspecified tic disorder. Tic disorders are common in China, with a prevalence of transient tic disorder (TTD), chronic tic disorder (CTD), and Tourette syndrome (TS) of 1.7, 1.2, and 0.3%, respectively (3).

Tics usually begin between the ages of 3 and 8 years and become worse between the ages of 8 and 12 years for most patients. The first tic symptoms are usually simple motor tics, restricted to one muscle or a single muscle group. Tics then progress to involve more muscle groups or present with mimicking. Simple vocal tics, demonstrating meaningless sounds, usually occur after motor tics. For children or adolescents, the features of tics wax and wane in severity and frequency, and new tic symptoms replace, combine with, or even exacerbate the old ones (4, 5). Academic stress and family pressure may increase the incidence of tic disorders among school-age children. Excessive attention from parents, ridicule from peers, or incomprehension from teachers contribute to the aggravation of tics. Despite reports that tics tend to mitigate spontaneously throughout adolescence and reach complete remission in early adulthood, tics do not always remit within a year in most children with recent-onset tic disorders, and recurrence may occur even after long-term remission among patients with CTD (6). Attention-deficit hyperactivity disorder, obsessive-compulsive disorder, and autism spectrum disorder are the most common psychiatric comorbidities that impair social, behavioral, or emotional functioning (7).

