## 2. Methods and analysis

### 2.1. Study design and participants

This is a matched-pairs design, controlled, clinical trial with two groups (experimental group and healthy control group). Patients with tic disorders and age–gender-matched healthy children will be recruited through advertisements posted on web pages and display boards or through the outpatient system recommended by doctors at Panyu Hospital of Chinese Medicine (Guangzhou, China) and Foshan Fosun Chancheng Hospital (Foshan, China). Both hospitals are tertiary hospitals. All participants will be screened according to the inclusion and exclusion criteria. The guardians of eligible participants will sign a written informed consent (see Supplementary material 1) after a detailed explanation of the study by the investigators and will be provided with a baseline assessment. Participants are free to withdraw from the study at any time. This protocol was designed according to the Standard Protocol Items: Recommendations for Interventional Trials (SPIRIT) guidelines (42) and the Standard Protocol Items for Clinical Trials with Traditional Chinese Medicine 2018: Recommendations, Explanation, and Elaboration (SPIRIT-TCM Extension 2018) (43). The study was registered in the Chinese Clinical Trial Registry (ChiCTR2200057723).

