### 2.2. Eligibility criteria

Participants must fulfill the diagnostic criteria for provisional tic disorder and persistent motor or vocal tic disorder according to the DSM-5 (2). Patients will be screened according to the inclusion and exclusion criteria listed in Table 1.

**Table 1 T1:** Eligibility criteria.

	**TD patients**	**Healthy controls**
Inclusion Criteria	1. Aged between 4 and 18 years	1. Matched age, sex, family history of a psychiatric condition, parental marital status, mode of delivery and birth weight to the TD group^*^
	2. Meeting the diagnostic criteria of transient tic disorder and Persistent Motor or Vocal Tic Disorder according to the Diagnostic and Statistical Manual of Mental Disorders, Fifth Edition (DSM-5) (1, 2)	2. No current or history of head trauma, convulsions, epilepsy, growth and development disorders, mental illness, digestive system disease, abdominal operation or asphyxia at birth
	3. The course of a provisional tic disorder is more than 3 months	3. No current or history of medication of mental disorders especially drug influencing neurotransmitters
	4. The score of YGTSS >12	4. The mother is healthy during pregnancy (no history of infection, digestive system disease, trauma or taking any medication)
	5. Have not received acupuncture or moxibustion within 3 months, and drug withdrawal period ≥12 weeks	
	6. Guardians are willing to sign the informed consents	
Exclusion Criteria	1. Secondary tic disorders	
	2. Patients with severe diseases of important organ systems: liver and kidney damage, cardiovascular insufficiency, metabolic diseases, malignant tumors, etc., which may adversely affect our clinical observation	
	3. Obsessive-compulsive disorder, depression, Attention deficit hyperactivity disorder, anxiety, autism spectrum disorder, eating disorder, or a history of substance abuse	
	4. Epilepsy, Huntington's disease, rheumatic chorea, hepatolenticular degeneration, substantia nigra degeneration, psychogenic tics and other extrapyramidal disorders	
	5. The use of antibiotics, probiotics, high-dose vitamin or immunomodulatory medications within 4 weeks before the fecal sample collection	
	6. Conditions like any infective diseases or other severe disorders that may influence the gut microbiota	
	7. Ulcers or surgical scars on the acupoint area	
	8. Children who are participating or participated in other clinical trials within 1 month	

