**Figure 4 F4:**
[figure not shown]
Location of acupoints.

We aim to apply QH needles (patent no. ZL2015 20271867.0; 0.3 × 0.13 × 30 mm; QH; Chongqing Figure 3) in the acupuncture treatment. Manipulation (48) will be done as follows. After skin disinfection, the QH needles will be inserted vertically into the myofascial. Then, the needle will be directed toward the diseased site, and its handle will be gently moved from side to side at an angle of 15–30. When the “de qi” sensation (feelings of numbness, tingling, swelling, soreness, or muscle weakness) becomes obvious (~10 s after stimulation), the needle will be withdrawn. The pinholes will be pressed with a sterile, dry cotton ball without needle retention. As for the Baihui acupoint, the needle will be inserted perpendicularly into the galea aponeurotica, then withdrawn slightly, and the abovementioned manipulation will be performed. As for the Yintang acupoint, the needle will be inserted obliquely into the subcutaneous, and the abovementioned manipulation will be performed.

Participants in the experimental group will receive eight sessions of acupuncture treatment (two times a week for 4 weeks), and participants in the healthy control group will not receive the intervention.

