## 4. Machine learning model on acupuncture response prediction

We will develop a machine-learning model to predict the acupuncture (QH needle) response. Transfer learning will be adopted. 16S rRNA, serum metabolomics, and clinical profile data will be downloaded from published data or public databases as source domains to generate a deep neural network (DNN) model. Data from the present study are set as the target domain to fine-tune the DNN model. An additional file shows the method in more detail (see Supplementary material 2).

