## 5. Discussion

This is a matched-pairs design, controlled, clinical trial to investigate how QHN therapy relieves tic disorders *via* the modulation of gut microbiota and serum metabolites. To the best of our knowledge, the management of tic disorders is largely through psycho-behavioral therapy, which is not easy to access in many developing countries. Medicine is usually not the optimal selection because most patients are children. A search for a feasible and economic therapy for tic disorders should be promoted.

Acupuncture, as traditional Chinese medicine, has been widely accepted for its ready availability and lower cost. Its clinical efficacy in the treatment of pediatric neurological diseases, including cerebral palsy, autism spectrum disorders, and intellectual delay, has been proven. In addition, a growing body of research has proven that acupuncture shows good results in relieving tic symptoms, reducing recurrence rates, and causing fewer adverse events.

The main acupoints selected in the present protocol are under the sinew meridian theory based on traditional acupuncture. Tic disorders are categorized as meridian sinew disorders, and their pathogenesis is that qi and blood fail to nourish meridian sinew, resulting in trembling of the tendons and muscles, tics, and contractures. GV20 and EX-HN3 are the acupoints of the governor vessel that is located on the head or face. The governor vessel communicates with and governs all the yang meridians and runs into the brain. The three-foot yang and three-hand yang sinew channels start from four extremities and end at the face or the angle of the forehead. Acupuncturing at GV20 and EX-HN3 adjusts the yangqi of the entire human body and warms and nourishes the sinews. Furthermore, GV20 and EX-HN3 are widely used in neurological diseases, and it is reported that these two acupoints have positive effects in regulating neurotransmitter levels (52). BL14 is adjacent to the course of the meridian sinews of foot taiyang. Acupuncturing at BL 14 restores the balance of yangqi in meridian-sinews and is a transport point for the pericardium. It has been reported that BL14 is used in the treatment of tic disorders (53).

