In addition, to improve the clinical practice of acupuncture, we will further construct a prediction model based on multi-omics data and clinical profiles. Considering the small sample size, we will attempt to use the transfer learning method to develop a prediction model for personalized acupuncture treatment. Transfer learning is used to transfer knowledge from a generalized model to a more domain-specific model. It would enable the utilization of biological data published in the literature and reduce the demand for data collection when investigating new processes. Rogers et al. (55) showed that transfer learning is a highly data-efficient technique to predict the modeling of bioprocesses, a typically low-dimensional, small-data problem, but its usage in the biomedical field is scarce. In the present study, we will extract generalizable knowledge from well-understood published biological data, capturing essential process mechanisms to set a source model. We will then apply this understanding to characterize and screen novel samples and refine the model with our data. Our study is a new attempt to develop a prediction model for personalized acupuncture treatment.

Because most participants enrolled are school-aged children, they may have class during normal working hours, which may affect timely treatment. Therefore, we will make an appointment with parents after enrollment and keep in touch with them every week during the treatment sessions. In addition, we will do a 6-month follow-up to reduce the number of patients lost to follow-up. We will also maintain contact with the parents *via* WeChat or telephone and follow up through these channels.

This study has some limitations. There have been no acknowledged biomarkers for the assessment of tic severity. The rating of YGTSS is based on clinical experience in working with patients with tic disorder and their families, which is probably subjective. The sample size is small, and the follow-up duration is not very long.

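### The trial is called controlled, but its only controls are healthy children and the primary YGTSS change is tested within the treated group alone, so a significant result cannot be credited to the therapy

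*Protocol article*

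**What the plan says.** Section 2.1 gives the design: "This is a matched-pairs design, controlled, clinical trial with two groups (experimental group and healthy control group"). The Abstract and the opening of Section 5 use the same label, and the Abstract speaks of participants being allocated to the groups.

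Membership in fact follows disease status. Table 1 requires of the controls: "No current or history of head trauma, convulsions, epilepsy, growth and development disorders, mental illness, digestive system disease, abdominal operation or asphyxia at birth". Section 2.4.1 adds that "participants in the healthy control group will not receive the intervention". No untreated, waiting-list or sham group of children with tics is described.

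The primary outcome is the change in YGTSS from baseline to 4 weeks (Sections 2.5 and 2.5.1). Its analysis is in Section 3.1.1: "Changes in YGTSS, GSI, and concentration of serum zonulin in the experimental group before and after treatment will be analyzed using paired sample" t-tests, with the Wilcoxon signed-rank test as fallback, two-sided at 0.05. The only comparison between groups in that section is zonulin at baseline.

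The aims are causal. The end of Section 1 wants to establish how the therapy works. Section 3.3.2 looks for its therapeutic targets. Section 5 sets out "to investigate how QHN therapy relieves tic disorders". The limitations paragraph in Section 5 names the lack of accepted biomarkers, the subjectivity of the rating and, in its last sentence, "The sample size is small, and the follow-up duration is not very long". It does not name the absence of untreated children with tics.

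**The concern.** In a controlled trial, the control group shows what would have happened to the outcome without the treatment. Here it cannot. Healthy children have no tics to fluctuate, and they do not enter the primary test. Matching on age, sex, family history and birth factors does not change this.

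The article supplies the rival explanations. Section 1 says of children and adolescents that "the features of tics wax and wane in severity and frequency". The YGTSS draws on answers from parents or guardians, who know that the child is being treated, and Section 5 calls the rating probably subjective. Entry requires a score above 12 on the same scale as the outcome. Each of these can move the within-child difference with no effect of needling.

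At stake is what the trial may conclude. A question about how a therapy relieves tics presupposes that it does. If the fall in YGTSS cannot be credited to the therapy, before-after changes in GSI, zonulin, flora and metabolites cannot be read as its mechanism either.

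**Working it through.** **The plan's own figure.** Section 2.3 asks for at least 15 per group and allows 20% dropout. 15 / (1 − 0.20) = 18.75, so 19. The plan recruits 20, which leaves 20 × 0.80 = 16 completers. The figure is consistent. The 15 comes from earlier literature, with no effect size, SD or power, so nothing in it bears on what the paired test can show.

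**What each group contributes**

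| Quantity | Treated children with tics | Healthy controls | Untreated children with tics |
|---|---|---|---|
| YGTSS change (primary) | paired test | not in the analysis | none exist |
| GSI change | paired test | not in the analysis | none exist |
| Zonulin | paired test; baseline comparison | baseline comparison | none exist |
| Metabolites (Section 3.3.2) | compared with controls | compared with patients | none exist |

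The last column is the one that a treatment effect needs.

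**How often the planned test is significant with no treatment effect.** Let d be the mean change that would occur without treatment, in SDs of the change score. The paired t statistic is noncentral t with n − 1 degrees of freedom and noncentrality d√n, so

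P(significant) = 1 − F(t₀.₉₇₅; n − 1, d√n) + F(−t₀.₉₇₅; n − 1, d√n).

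The documents give no SD, expected change or natural-course rate, so d is an assumption and is shown over a range:

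| d (assumed) | d√16 | n = 16 | d√20 | n = 20 |
|---|---|---|---|---|
| 0 | 0 | 5% | 0 | 5% |
| 0.2 | 0.80 | 12% | 0.89 | 14% |
| 0.3 | 1.20 | 20% | 1.34 | 25% |
| 0.5 | 2.00 | 47% | 2.24 | 57% |
| 0.8 | 3.20 | 85% | 3.58 | 92% |

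The chance rises with n: a larger sample makes the misreading more likely.

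**Regression to the mean, only if the entry score is also the baseline.** The expected fall is (1 − r) × SD × φ(z) / (1 − Φ(z)), with z = (12 − mean) / SD and r the test-retest correlation. By simulation under three assumed pairs (mean 15, SD 8; mean 20, SD 10; mean 25, SD 10) and r from 0.5 to 0.85, the mean fall is about 0.3 to 2.3 points. With 16 completers the test is then significant in about 6% to 21% of trials. If baseline is a fresh rating taken after eligibility is settled, most of this disappears.

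**The case against.** The strongest defence is that the study does not pretend to be a randomised efficacy trial. Section 2.3 calls it exploratory, the Abstract says that it may elucidate a mechanism, Section 1 speaks of possible correlations, and the sentence that says controlled also says that the controls are healthy. Healthy children are a sound reference for zonulin and omics at baseline. All of this stands. It does not reach the primary outcome, though, and it sits beside aims worded as cause and effect. Nor could a statistical analysis plan supply the missing comparator.

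Several stronger readings are tempting, and the documents do not support them:

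- **That regression to the mean is built in.** Section 2.1 places a baseline assessment after screening. It does not say whether the YGTSS is rated again there, so reuse of the entry score is possible but not established.
- **That the rater is unblinded.** Section 2.5.1 names an experienced paediatric clinician, and Section 2.4 has one acupuncturist deliver the treatments. Masking of the rater, for example to visit, is not described either way. Subjectivity of the rating is already a listed limitation.
- **That tics would remit within 4 weeks.** Section 1 ties spontaneous improvement to adolescence and adds that recent-onset tics often persist beyond a year. Only short-term fluctuation is supported.
- **That the prediction model is mislabelled.** Section 4 says "We will develop a machine-learning model to predict the acupuncture (QH needle) response". Without untreated patients it can learn only outcome after treatment. However, the details are left to a supplement that is not shown, and the point does not depend on the name.

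**Conclusion.** The concern holds in this form: the label and the aims claim more than the design can identify. The primary analysis is a one-group before-after test, and the healthy controls cannot serve as its comparator. A significant fall in YGTSS would show that scores fell over 4 weeks, not why.

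The size is illustrative. With no treatment effect and an assumed untreated change of 0.2 to 0.8 SD of the change score, the test is significant in about 12% to 85% of trials with 16 completers and 14% to 92% with 20, against a nominal 5%. A reader might take one of these as the trial's actual false-positive rate. It is not, because the documents give no figure that fixes the untreated change. A reader might also infer that the therapy does not work. Nothing here bears on that; the design leaves the question open.

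This should be put right, because it concerns the primary outcome, carries into the mechanistic aims, and is absent from the stated limitations.

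**What to change.** 1. In the Abstract, Section 2.1 and the opening of Section 5, describe a single-group before-after study of treated children with tic disorders, with a matched healthy reference group. Drop the description as a controlled trial of the therapy.
2. In Section 3.1.1, report the mean within-patient YGTSS change with its 95% CI, and state that it does not estimate the effect of the therapy.
3. Reword the aims at the end of Section 1, in Section 3.3.2 and in Section 5 from cause to association.
4. Add the absence of an untreated tic comparator to the limitations paragraph in Section 5.
5. The text of Section 2.5 does not make clear whether controls also give week-4 samples. If they do, report patient change minus matched-control change for zonulin and the omics measures. This removes calendar and batch drift shared by both groups, but not fluctuation specific to the patients.

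Items 1 to 4 are wording and one interval, and item 5 is one further analysis of samples already taken. None needs more patients, so all remain possible although recruitment is under way (Section 3.5). The price is a weaker headline claim.

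Only a concurrent group of children with tics who do not receive the therapy would identify an effect, and that would be a different study. By the normal approximation, at assumed standardised differences of 0.5, 0.8 and 1.0, 16 completers per arm give 29%, 62% and 81% power, and 80% power needs 63, 25 and 16 per arm.
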